#### Secondary study outcomes

Secondary study outcomes, assessed at baseline and follow-up include parent-reported mental health, daily functioning, well-being and sleep quality; beliefs, intentions and engagement in self-care activities; parenting stress, sense of competence and parenting behaviours; and family functioning.

*Depression Anxiety and Stress Scale (DASS-21)*[53] assesses the negative emotional states of depression, anxiety and tension or stress over the past week. Items are rated on a 4-point scale ranging from 0 = *Does not apply to me at all* to 3 = *Does apply to me very much or most of the time*. Response are summed and multiplied by 2 to obtain a total score for each scale. Higher scores indicate greater symptoms on that scale; recommended cut-off scores for severity labels (normal, moderate, severe and extremely severe) are given in the DASS manual.

*Profile of Mental States (PoMS)*[54] is an adjective checklist of six mood factors, designed to measure mood variations over time in psychologically normal populations. Three subscales from the PoMS were used in this study: Anger – Hostility which assesses irritability (12-items); Confusion-Bewilderment assesses clarity of thought (7-items); and Vigour-Activity assesses energy and alertness (8-items). Participants rate their responses to each of the adjective items on these subscales on a 5-point scale and responses are summed to give a total score for each of the three subscales. Community norms for the PoMS subscales are available, and the PoMS has been widely used in research around Australian community samples during early parenting.

*Pittsburgh Sleep Quality Index (PSQI)*[55] is a standardised assessment of the overall quality of sleep. Two subscales from the PSQI were used in this study to assess participants’ sleep quality: a global rating of overall sleep quality, and the two item assessment of ‘daytime dysfunction’, assessing the degree to which fatigue impacts upon routine daily function and tasks. Two additional items have been added to ask parents about the reason for sleep disruption. Items are rated on a 4 point scale (0 = *Not during the past month* to 3 = *Three or more time a week*), where higher scores indicate poorer sleep quality.

*Beliefs about Self-Care Survey*[47] was designed specifically for this project, and is based on Ajzen and Fisbein’s Theory of Planned Behaviour/Reasoned Action. The items assess parents’ attitude toward self-care behaviour (10-items); peer and social norms influencing their thoughts about the self-care behaviour (4-items); and identifying barriers to engaging in self-care behaviour (10-items). Participants rate their response to each of the survey items on a 7-point scale, ranging from 7 = *Strongly Agree* to 1 = *Strongly Disagree*.

*Health and Self-care Behaviour*[47] consists of three items which ask respondents to rate the quality of their diet, their overall level of physical activity and the extent to which they engage in self-care behaviours such as relaxation, taking time out, and pursing hobbies on a 7-point Likert scale, ranging from 1 = *Strongly Disagree* to 7 = *Strongly Agree*.

*Parenting Sense of Competence Scale (PSOC)*[56] is a 16-item self-report measure that was used to assess parents’ satisfaction and efficacy in their parenting role. The Satisfaction subscale assesses parental motivation versus parenting frustration and anxiety. Items are rated on a 6-point Likert scale (1 = *strongly agree* to 6 = *strongly disagree)*. High scores on both subscales indicate high degrees of satisfaction and efficacy in parenting.

*The Parenting Stress Index (PSI)*[57] is a widely-used self-report assessment of the total stress parents experience within the daily interactions of parenting in the early years. Only the Difficult Child and Parent–child Dysfunction subscales were used; the Difficult-Child subscale reflects sources of parental stress associated with child characteristics that make it difficult to fulfill the parenting role, while the Parent–child Dysfunction subscale reflects parental stress associated with dysfunction in the parent–child relationship. Each subscale consists of two items, rated on a 5-point Likert scale (1 = *strongly agree* to 5 = *strongly disagree*). Higher scores indicate higher stress in the respondents role as a parent, while lower scores may be related to low stress, or dysfunctional parent–child relationships.

*Parenting Practices - Hostility and Warmth.* These items were taken from the Growing Up in Australia: Longitudinal Study of Australia Children
[58]. Parental warmth refers to expressions of affection, showing interest and enjoyment in the child’s interests and activities; while Parenting hostility refers to anger and losing temper with the child. These parenting behaviours are of particular interest in the current study as they have been linked to a broad range of psychosocial, developmental and behavioural outcomes for children
[59-63]. Participants rate 11-items (warmth, 6-items; hostility 5-items) on a 5-point Likert scale, ranging from 1 = *Never/Almost Never* to 5 = *Always/Almost Always*. Higher scores on each subscale indicate higher parental warmth and greater parental hostility.

The *Family Assessment Device (FAD)*[64]*.* The General Functioning scale from the FAD was used in the current study. This assesses the overall health and function of the family. The 12-items are rated on a 4-point scale, ranging from 1 = *Strongly Agree* to 4 = *Strongly Disagree*. The higher the score the more problematic the participant perceives their family’s overall functioning.

*Resources and support.* This part of the survey asked parents to indicate which support services or resources they have accessed since their baby was born. This is asked because we would like to be able to control or account for the types of support parents have accessed. Furthermore, it allows us to address in analyses any ‘contamination’ in the waitlist control group via exposure to WAP resources.

#### Satisfaction survey

Upon completing the intervention, participants in the written information and written information with telephone support groups were given a ‘satisfaction survey’ to evaluate the program. The satisfaction survey comprised of 14-items, which assessed the relevance and satisfaction with the program content and delivery method on a 5-point scale ranging from 1 = *Strongly Disagree* to 5 = *Strongly Agree*. Additionally, there were two open-ended items that allowed parents to discuss what they liked most about the program and ideas on how to improve the program.

### Procedures

Following initial contact, interested parents were assigned a participant identification code to protect confidentiality of all data provided, and an information pack. The pack contained a plain language statement, consent form, and the baseline questionnaire. If the parent was willing to participate they were able to return the hardcopy consent form and baseline questionnaire via reply paid envelope or could complete it online via a secure, web-based survey provider, indicating written consent on the form provided in the electronic survey. Two reminder calls, two weeks apart, were placed to parents who had not returned their baseline information. Those who did not return data following these calls were considered to have declined to participate.

Once the consent form and baseline surveys were received, participants were randomly allocated to one of the study groups, and were notified of which group they were randomised to. If the participant was allocated to the written information with telephone support group, a home visit was scheduled during this telephone call. If the participant was allocated to the written information only group, the intervention resources were posted out immediately after the telephone call. Participants who were randomised to the waitlist group were informed that they would not have access to the study intervention straight away but have the option of receiving either the written information only or the written information with telephone support upon receiving their final questionnaire in three months’ time.

Follow-up questionnaires were posted out to participants at two weeks, and six weeks following completion of the intervention for those in the intervention arms, and at six and 12 weeks for those in the control arm. Participants in either intervention arm were prompted to complete the satisfaction survey either during their last telephone session, or via phone, one month following provision of the WAP workbook, for those in the written only condition. In order to minimize study drop-out, researchers called participants if they had not returned their follow-up questionnaires at two and four weeks after they were mailed out to them. Control participants were advised that they would be contacted once their final survey was received and would be offered the WAP intervention.

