#### Written information with telephone support condition

Participants in this arm received professionally-led, structured guidance to supplement the written information provided in the WAP booklet, over the four weeks of the programme. Parents received an initial home visit from a trained facilitator. The purpose of the home visit was to establish rapport with the parent, provide a WAP workbook, introduce the program and work through the first section of the workbook. At the home visit, three telephone sessions were scheduled at weekly intervals for the following three weeks, corresponding with one per session of the workbook. During the telephone sessions, the facilitator checked the parent’s understanding of the workbook content, clarified any information, answered questions, or guided progress through the material when necessary. Parents were encouraged to think about specific strategies relevant to their needs, to address barriers to these strategies, to develop goals, and ultimately, devise a plan to support them with the management of fatigue.

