### Data analysis

A range of descriptive and multivariate data analyses will be used to assess the aims of the study. Descriptive statistics will be presented of the demographic characteristics of the sample. Means and standard deviations will be given for continuous outcomes, as well as medians and inter-quartile ranges where continuous data are skewed. Frequencies for categorical data will be reported. A mixed-design analysis of variance (split-plot ANOVA) will be conducted to compare the intervention and control conditions (between-subjects factor) on each of the primary and secondary outcomes at pre, post and follow-up (within-subjects factor). Effect sizes will be reported where appropriate, with 0.01, 0.06 and 0.14 as small, medium and large effect sizes for multivariate *η*^2^, while 0.2, 0.5 and 0.8 are small, medium, and large effect sizes for Cohen’s *d.* Finally, intention-to-treat analysis will be conducted using the last observation carried forward method for the missing post-intervention and follow-up data.

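### Follow-up is timed from completion of the programme in the intervention arms but from fixed weeks in control, so its timing, and on a literal reading its dispatch, depends on adherence after randomisation

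*Protocol article*

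**What the plan says.** All references are to the protocol article.

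- **Follow-up rule, intervention arms (Procedures):** "Follow-up questionnaires were posted out to participants at two weeks, and six weeks following completion of the intervention for those in the intervention arms".
- **Follow-up rule, control (Procedures):** "and at six and 12 weeks for those in the control arm". The starting point is not spelled out. Waitlist parents are told at allocation that their final questionnaire comes in three months, which fits 12 weeks from allocation.
- **Start of the supported arm (Procedures):** "a home visit was scheduled during this telephone call", that is, the call announcing the allocation.
- **Content of the supported arm (Written information with telephone support condition):** the facilitator's tasks at the visit include to "provide a WAP workbook, introduce the program and work through the first section of the workbook". Then: "At the home visit, three telephone sessions were scheduled at weekly intervals for the following three weeks". Support runs "over the four weeks of the programme".
- **Start of the written-only arm (Procedures):** "the intervention resources were posted out immediately after the telephone call". The workbook is meant for four weeks of self-directed use.
- **Reminders (Procedures):** calls to non-returners are counted from the date of mailing.
- **Missing outcomes (Data analysis):** after a split-plot ANOVA over three time points, "intention-to-treat analysis will be conducted using the last observation carried forward method".

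**The concern.** Control is followed by the calendar. The intervention arms are followed from an event that happens after randomisation and that, in the supported arm, depends on what the parent does. The home visit is where the workbook is handed over and the calls are booked. A parent who never has the visit gets neither, and so reaches no completion date. A parent who stops after one call does not reach one either. The reminder calls do not help, because they start only once something has been mailed.

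Two things are at stake. First, outcomes in the supported arm may be measured at a different time since allocation from those in control, by an amount that varies with uptake. Secondly, if the rule was followed literally, some supported-arm parents would have no follow-up outcome although they could have been reached by post. Either would sit badly with an intention-to-treat analysis. It would also bear on the third hypothesis, which compares the supported with the written-only arm.

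**Working it through.** **1. Timing at nominal length.** Inputs: four-week programme; offsets of 2 and 6 weeks; control at weeks 6 and 12, taken as weeks from allocation. With no delay, 4 + 2 = 6 reproduces the first control date, and 4 + 6 = 10 compares with control week 12. That second gap is a separate point.

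**2. Timing when the home visit is delayed.** The documents give no visit delays; the values here are assumptions. Weeks since allocation = delay + programme length + offset. Length is 4 weeks if completion means the end of the programme, or 3 weeks if it means the third weekly call after the visit.

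| Assumed delay (weeks) | Follow-up, 4-week reading | Follow-up, last-call reading | Control |
|---|---|---|---|
| 0 | 6 / 10 | 5 / 9 | 6 / 12 |
| 1 | 7 / 11 | 6 / 10 | 6 / 12 |
| 2 | 8 / 12 | 7 / 11 | 6 / 12 |
| 4 | 10 / 14 | 9 / 13 | 6 / 12 |

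On either reading the supported-arm dates move with uptake and the control dates do not.

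**3. What marks completion.** The article gives no definition. The nearest evidence is the satisfaction survey, given once the programme is finished. Procedures places its prompt in the last telephone session for the supported arm, and one month after provision of the workbook for the written-only arm. For that survey, then, completion is a contact event in one arm and elapsed time in the other. The article does not say that the follow-up questionnaires use the same clocks.

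**4. Direction of bias if non-starters get no questionnaire.** All inputs are assumed. A share q of the supported arm never starts and gains nothing from the programme; starters gain 0.5 SD over control; parents without the programme improve by c SD.

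- Effect over all randomised parents: (1 − q) × 0.5.
- Completers only: 0.5.
- Baseline carried forward: (1 − q)(c + 0.5) − c.
- Carried forward minus all randomised: (1 − q)c − c = −q × c.

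| q | All randomised | Completers only | Carried forward, c = 0.2 |
|---|---|---|---|
| 10% | 0.45 | 0.50 | 0.43 |
| 20% | 0.40 | 0.50 | 0.36 |
| 30% | 0.35 | 0.50 | 0.29 |

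Completers-only analysis overstates the effect here. Carrying baseline forward understates it when untreated parents improve (c > 0), is neutral when they do not change (c = 0), and overstates it when they worsen: with q = 20% and c = −0.2, the difference is +0.04. The sign therefore depends on the analysis and on the untreated course.

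**The case against.** The strongest reply is that the article states when questionnaires go out and does not restrict who receives them. Completion can be read as the end of the scheduled four weeks, and a rule for parents who never start is a detail that a condensed article may leave to the full protocol. This stands as far as it goes: a reader might infer that non-completers were not followed, and the text does not say so. It does not remove the timing problem, because even the nominal four weeks start from a home visit with no fixed date.

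A reader might also infer that attrition depends on adherence in the supported arm alone. The text does not establish that. One sentence covers both intervention arms. Reading completion literally in one and as elapsed time in the other relies on the satisfaction-survey clock. Read literally in both, written-only parents who do not finish the workbook also lack a date.

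Finally, a reader might put a figure on a bias favouring the supported arm. If 10–30% do not complete and their follow-up fatigue is 0.3–0.5 SD worse, the shift in observed means is 0.10 × 0.3 = 0.03 to 0.30 × 0.5 = 0.15 SD. With 61 per arm, the standard error is √(2/61) = 0.181 SD, so shifts of 0.10 and 0.15 SD would raise a two-sided 5% test to about 8.5% and 13%. The arithmetic is right, but both inputs are assumed. It also uses raw follow-up means, whereas the planned ANOVA uses change over time, in which a stable difference in fatigue cancels. It supposes that all non-completers are lost while equally tired parents in other arms respond. And with baseline carried forward these parents stay in the analysis, where the direction can reverse.

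**Conclusion.** The point holds as a weakness in a stated rule. Follow-up is tied to an event in the intervention arms and to the calendar in control. In the supported arm the event depends on uptake and adherence after randomisation, and parents who never start or who stop early have no completion date under the rule as written. The intention-to-treat promise does not cure this. Carrying baseline forward keeps such parents in that analysis, but with a substituted value where a real one could have been collected; the split-plot ANOVA named before it conventionally needs all three measurements.

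Neither the size nor the direction of any bias can be derived, because the article gives no adherence, visit-delay or arm-specific attrition figures. The tables above are illustrations under assumed inputs. The stronger statements, that non-completers were left unfollowed or that the supported arm is flattered, are not supported. The correction is worth making because it removes the dependence on adherence under either reading of completion.

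**What to change.** Set both questionnaire dates from allocation, at the same intervals in every arm: for example, allocation plus the nominal four weeks plus 2 and 6 weeks, that is weeks 6 and 10. Post them to every randomised parent who has not withdrawn from follow-up, whether or not the visit or calls took place. For parents already allocated who have no completion date, use the nominal date. Record sessions received as adherence data only, never as a condition for follow-up.

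The direct cost is a change of wording, a change to the mailing schedule and a few extra questionnaires. There are three downsides.

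- The interval since a parent's own last session will vary. With a two-week wait for the visit, week 6 falls at the end of the programme (2 + 4 = 6) rather than two weeks after it.
- The labels of 2 and 6 weeks post intervention in the Hypotheses become nominal.
- The article says that recruitment is complete and that delivery and data collection are ongoing, so parents already followed under the old rule will have somewhat different timing. The actual date of each questionnaire, counted from allocation, should be recorded.

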### Intervention

#### Written information condition

Parents allocated to the WAP written information group were sent the WAP intervention workbook. The 44-page workbook is broken into four parts designed to be used in a self-directed manner over a period of 4-weeks. The first part provides information about fatigue and exhaustion, including what it is, how it can affect parents, and why it occurs. The second part provides tips for charging up and includes strategies such as taking time out for self, helpful thinking, sleeping better and resting, eating well, and keeping active. The third part provides tips for saving energy and includes strategies such as prioritising, problem solving, and getting support. Throughout these sections of the workbook are activities to help parents think about ways to apply the strategies and make them relevant to their individual needs. The notion of developing a goal and plan to make it happen is also emphasized. The final part of the workbook then provides advice on how to make the plan work and contact information and websites for additional support services parents may choose to pursue.

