#### Primary study outcome

Primary study outcomes are parent-reported symptoms of fatigue, assessed at baseline and at short- (2 weeks) and longer-term follow-up (eight weeks).

*Fatigue Assessment Scale (FAS)*[50] is a ten item measure that will be used to assess the physical and cognitive symptoms of fatigue. The items are rated on a 5-point scale, ranging from 1 = *Never* to 5 = *Always*, with higher scores indicating higher levels of fatigue. The scale is reported to have good psychometric properties, and has been evaluated for use with parents
[35].

*Fatigue Severity Scale*[51,52] assesses fatigue intensity and functional limitations caused by fatigue. The nine items (e.g., “Fatigue interferes with my work, family, or social life”) are rated on a 7-point scale, ranging from 1 = *Strongly Disagree* to 7 = *Strongly Agree*. Higher scores reflect higher levels of fatigue.

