### Hypotheses

Firstly, we hypothesised that compared to a waitlist control condition, parents receiving either form of the intervention will report the following short-term outcomes at 2-weeks post intervention:

a) Stronger beliefs and intention about engaging in self-care behaviour.

b) Higher levels of self-care behaviour.

c) Lower levels of fatigue and daytime dysfunction.

d) Lower levels of irritability, improved vigour and clarity of thought.

e) Improved sleep quality.

f) Lower levels of parenting stress and parenting hostility, and higher levels of parental warmth.

Secondly, we hypothesised that compared to a waitlist control condition, parents receiving either form of the intervention will report the following longer-term outcomes at 6-weeks post intervention:

a) Higher levels of parental self-efficacy.

b) Lower levels of depression, stress and anxiety.

c) Higher quality of the couple relationship and parent–child interactions.

Finally, we hypothesised that compared to the written information only condition, the intervention effects will be significantly stronger for parents in the written information with telephone support condition.

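### The second follow-up is dated both six and eight weeks after the programme; on the six-week schedule, intervention parents are assessed about two weeks earlier than controls

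*Protocol article*

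**What the plan says.** Both active programmes are described as four weeks long. The workbook is "designed to be used in a self-directed manner over a period of 4-weeks" (Written information condition), and the supported version runs "over the four weeks of the programme" (Written information with telephone support condition).

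The follow-up timing appears in four places:

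- Procedures, intervention arms: "Follow-up questionnaires were posted out to participants at two weeks, and six weeks following completion of the intervention for those in the intervention arms". Procedures, control arm: "at six and 12 weeks for those in the control arm".
- Abstract, Methods/design: two and six weeks after the intervention.
- Hypotheses: the second set concerns "longer-term outcomes at 6-weeks post intervention".
- Primary study outcome: fatigue is "assessed at baseline and at short- (2 weeks) and longer-term follow-up (eight weeks".

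Procedures does not state when the control clock starts. It does say that waitlist parents were told, when notified of their allocation, to expect the final questionnaire about three months later, so the 12 weeks evidently run from about allocation. Under Data analysis, the pre, post and follow-up assessments form one within-subjects factor shared by all arms.

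**The concern.** One visit of the primary outcome carries two dates, and the dates differ in their consequence. Under one of them the intervention arms and the control arm are measured at different times after allocation. That difference would follow arm, so randomisation would not balance it: infant age is balanced at entry but not at the second assessment. Any outcome that changes over the early months would then carry some ordinary change into the between-arm contrast.

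The contrasts exposed are the second hypothesis set (self-efficacy, depression, anxiety and stress, couple and parent–child relationship) and longer-term fatigue. The ANOVA described would not reveal the problem, because it labels both assessments as the same follow-up. The protocol makes time-dependence plausible: its Background ties parental fatigue to infant night waking and to sleep changes around birth.

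**Working it through.** **Inputs**

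- Programme length: 4 weeks in both intervention arms (Intervention section).
- Start delay: about 0 in the written arm, since the workbook is posted straight after the allocation call (Procedures). In the telephone arm the home visit is only booked at that call; call the wait *d* weeks. Its length is not given.
- Interval after the programme: 2 weeks, then 6 (Abstract, Procedures, Hypotheses) or 8 (Primary study outcome).
- Control: 6 and 12 weeks, taken as running from allocation.

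**Formula:** weeks since allocation = start delay + programme length + interval after the programme.

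**Start delay 0**

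| Visit | Intervention arms | Control | Gap |
|---|---|---|---|
| First | 0 + 4 + 2 = 6 | 6 | 0 |
| Second, six-week text | 0 + 4 + 6 = 10 | 12 | 2 |
| Second, eight-week text | 0 + 4 + 8 = 12 | 12 | 0 |

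The control arm's 6 weeks is reproduced exactly. Its 12 weeks is reproduced only with the eight-week figure.

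**Interval between the two mailings:** six-week text, 6 − 2 = 4 weeks in the intervention arms against 12 − 6 = 6 in control; eight-week text, 8 − 2 = 6 against 6.

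**Reminders:** "researchers called participants if they had not returned their follow-up questionnaires at two and four weeks after they were mailed out to them". In the intervention arms the last reminder for the first questionnaire falls 2 + 4 = 6 weeks after the programme. Under the six-week text that is when the second questionnaire is posted; under the eight-week text it is two weeks before. In control it falls at 6 + 4 = 10 weeks, two weeks before the second mailing.

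**Telephone arm.** With a four-week programme, the second visit under the six-week text is at 10 + *d* weeks, so the gap to control is 12 − (10 + *d*) = 2 − *d*. A wait narrows the gap at this visit, and a two-week wait closes it. At the first visit the arm is at 6 + *d* against 6, so the same wait opens a gap of *d*.

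The end of this programme is itself loosely fixed, because "three telephone sessions were scheduled at weekly intervals for the following three weeks", which puts the last call three weeks after the home visit. Taking completion at 3 to 4 weeks and assuming *d* between 0 and 2 weeks:

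- first visit: 0 + 3 + 2 = 5 to 2 + 4 + 2 = 8 weeks (control 6);
- second visit, six-week text: 0 + 3 + 6 = 9 to 2 + 4 + 6 = 12 weeks (control 12);
- second visit, eight-week text: 0 + 3 + 8 = 11 to 2 + 4 + 8 = 14 weeks (control 12).

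**Bias:** gap in weeks × natural change per week. The protocol gives no rate of change for any outcome, so the product cannot be evaluated.

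**The case against.** The strongest reply is that the design is aligned and only the wording is wrong. Eight weeks makes the second visit 12 against 12, equalises the mailing intervals at 6 and 6, fits the three months quoted to waitlist parents, and removes the reminder overlap. Six could even have been meant as weeks after the first follow-up, since 2 + 6 = 8. This stands as a possibility. It is not established: six weeks after the intervention is stated in three of the four places, including the operational section.

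Four stronger readings are tempting, and the document does not support them:

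- *Arm is confounded with time.* This holds only if the six-week schedule was followed.
- *The bias, or the inflation of false positives, can be quantified.* Any weekly drift would be an assumption without a source, and zero cannot be excluded. The Background reports that untreated mothers' fatigue did not fall over time in a cited telephone trial, although those mothers were selected for difficult infants and the statement does not cover mood or parenting outcomes. The sign is also open: improvement with age would favour the later-measured controls and hide benefit, while worsening would exaggerate it.
- *Waiting for the home visit makes the second-visit gap worse.* It narrows it, as 2 − *d* shows. It shifts the telephone arm at the first visit instead, and relative to the written arm at both visits.
- *The powered comparison is compromised.* The sample size rests on two weeks after the intervention, which is nominally week 6 in every arm. The hypotheses on fatigue, sleep, irritability, parenting stress and hostility are also set there.

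**Conclusion.** The protocol contradicts itself on the date of its second follow-up, six weeks against eight, and this needs correcting on any reading. If Procedures was followed as written, that visit falls about 10 weeks after allocation in the intervention arms (later in the telephone arm by any wait for the home visit) and at 12 weeks in control. The offset is then about two weeks of elapsed time and infant age, which the planned ANOVA treats as a single occasion. If eight weeks was followed, the nominal offset is zero.

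This rests on a four-week programme starting at about allocation and on a control clock that also starts there; the latter is inferred, not stated. The effect on the results cannot be sized or signed from the document and may be small for fatigue. The consequence is confined to the longer-term contrasts. The two-week outcomes are touched only through a home-visit wait, which would also bear on the telephone-versus-written comparison.

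**What to change.** 1. Establish which schedule was used, and make the Abstract, Primary study outcome, Procedures and Hypotheses agree. State the event from which the control arm's 6 and 12 weeks are counted. This costs only text.
2. Recruitment is reported as complete and data collection as ongoing. Send every second questionnaire not yet posted at the same number of weeks after randomisation in all three arms. This is a change to the mailing list. If it departs from what earlier participants received, there will be two schedules, and the report should say who had which.
3. For questionnaires already returned, report the distribution of actual time from randomisation to completion by arm at both visits. This needs completion dates; the article does not say whether they were recorded.
4. Add a sensitivity analysis of the second follow-up using elapsed time or infant age at completion. A time-varying covariate does not fit the planned split-plot ANOVA, so this needs another model, such as a linear mixed model. Under the six-week schedule, elapsed time is largely collinear with arm, and what separates them is mainly how late parents return the form, which is self-selected. Infant age is less tied to arm because infants enter anywhere from 0 to 6 months, but its use assumes that differences in age between families stand for change within a family. Neither adjustment replaces aligned mailing.
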